## Methods/Design

### Study design

This trial is a pragmatic randomized and controlled study. A previous study conducted in our hospital demonstrated that needling at Fengchi (GB 20) was effective for the treatment of PCIV [8], but the optimal treatment parameters are unknown. This study protocol was approved by the regional ethics review board of Tianjin University of Traditional Chinese Medicine (approval number: TJUTCM-EC20110005). This trial is registered in the Chinese Clinical Trial Registry under the following identifier: ChiCTR-RTRCC-12002675. This trial will be performed in accordance with the principles of the Declaration of Helsinki (Version Edinburgh 2000). Informed consent will be obtained from each participant before enrolment. This work has not been published elsewhere.

### Randomization

Patients will be consecutively and randomly assigned to one of four groups in a 1:1:1:1 ratio. Randomization will occur before the first acupuncture treatment. A computerized random number generator will be used to generate the randomization sequence. Allocation concealment will be performed via sequentially numbered opaque, sealed envelopes by an investigator who is not involved in recruitment or assessment of the results.

### Blinding

The patients, outcome assessors, the statistician, data-handling personnel, transcranial Doppler operators, and carotid ultrasonography and metabolomics operators will be blinded during the study. However, the acupuncture practitioners will not be blinded. An inquiry will be performed to investigate whether the subjects were blinded to the treatment that they received.

### Acupuncture groups

We aim to explore the quantity-effect relationship among various acupuncture parameters rather than to demonstrate the effectiveness of Fengchi (GB 20) needling. Therefore, a sham control group will not be used. We will use a pragmatic design to directly compare four parameters.

### Recruitment strategies

This trial was created by the Ministry of Science and Technology of the People’s Republic of China and will be administered by the State Administration of Traditional Chinese Medicine of the People’s Republic of China. The study will be performed at the First Teaching Hospital of Tianjin University of TCM, which is named the National Clinical Research Centre of Acupuncture and Moxibustion. We will place notices on printed recruitment posters and electronic bulletin boards. Interested patients will be referred to specific researchers and will receive screening evaluations. Imaging diagnoses from Transcranial Doppler (TCD) will be used in this study. The subjects will receive a routine blood examination, routine urine and feces tests, liver and kidney function tests, and an electrocardiogram (ECG) before recruitment.

All patients who meet the terms listed above will be given time to decide whether to participate in the study. The patients must fully understand all details of the informed consent before signing. Patients satisfying the diagnostic criteria will be introduced to the acupuncturist.

### Diagnostic criteria

The diagnostic criteria for PCIV are in accordance with the WHO criteria [11]. Patients must experience dizziness or vertigo that may be accompanied by the following: acute unsteadiness or ataxia; unilateral or bilateral (or involving one side after the other) visual, motor or sensory disturbances; double vision; dysarthria or swallowing impairment; acute impairment of consciousness; or acute confusion. Patients must have TCD or magnetic resonance imaging results that indicate vertebrobasilar insufficiency.

### Eligibility

#### Inclusion criteria

Participants will be included if they meet all of the following conditions:Diagnosis of vertebrobasilar insufficiency.Aged between 40 and 75 years.Volunteered to participate in the acupuncture treatment and can cooperate with the treatment.Provide signed informed consent.

#### Exclusion criteria

Participants will be excluded if they meet any of the following conditions:Cerebral hemorrhage or bulbar paralysis.Aural or ocular vertigo.Systolic blood pressure greater than 180 mmHg and/or diastolic blood pressure greater than 120 mmHg.Glasgow Coma Scale score of less than 15 or Hasegawa’s Dementia Scale score of less than 27.5.Serious heart, liver, or kidney diseases, critical illnesses that require operation, pregnancy, lactation, or serious dysphrenia.Participation in another current clinical trial or participation in a clinical trial within 3 months of recruitment.

### Interventions

The interventions were designed by [name], an academician at the Chinese Academy of Engineering, who promotes the standardization of acupuncture manipulation.

Fengchi (GB 20) is located on the posterior neck, inferior to the occipital bone, in the depression between the origins of sternocleidomastoid and the trapezius muscles [12]. Additional points will be added based on individualized pattern diagnoses.

### Rationale for acupoint selection and different manipulations of Fengchi (GB 20)

According to TCM theory, Fengchi (GB 20) is one of the main acupoints that can be used to help treat vertigo. Studies have demonstrated that acupuncture at Fengchi (GB 20) can affect cerebral blood flow [8,13].

Based on the quantity theory of acupuncture manipulation [14], differences in manipulations at Fengchi (GB 20) may induce different clinical effects. We selected different directions (the contralateral outer canthus or the Adam’s apple) and different frequencies (60 times per minute or 120 times per minute) to investigate our hypothesis. Needling manipulations will be performed manually by one experienced (more than 20 years) acupuncturist. Before conducting this trial, the acupuncturist received professional training to ensure the accuracy of needling replication.

The four manipulations used in this study are often used in clinical practice. Some studies state that the direction of acupuncture at Fengchi (GB 20) should be toward the contralateral outer canthus [15]. However, other studies acupuncture at Fengchi (GB 20) toward the Adam’s apple [16]. The two frequencies were chosen based on clinical experience.

### Protocol for acupuncture manipulation

Sterile disposable stainless steel needles (length: 40 mm, diameter: 0.25 mm; Hwatuo, Suzhou Medical Supplies Factory Co., Ltd., Suzhou, China) will be used on patients. For the main acupoint, Fengchi (GB 20), each group will be needled with twisting for a minute. Group 1 will receive twirling with a frequency of 60 times per minute toward the contralateral outer canthus at a depth of 0.5 to 0.8 cun. Group 2 will receive twirling with a frequency of 60 times per minute toward the Adam’s apple at a depth of 0.5 to 0.8 cun. Group 3 will receive twirling with a frequency of 120 times per minute toward the contralateral outer canthus at a depth of 0.5 to 0.8 cun. Group 4 will receive twirling with a frequency of 120 times per minute toward the Adam’s apple at a depth of 0.5 to 0.8 cun (Figure 1). Additional points will be added based on individualized pattern diagnoses. For the retention of phlegm-dampness, we will add Fenglong (ST40), Zusanli (ST36), and Yinlingquan (SP9). For hyperactivity of Liver Yang, we will add Taichong (LR3) and Taixi (KI3). For deficiency of Kidney Yin, we will add Taixi (KI3), Zhaohai (KI6), and Neiguan (PC6). For blood stasis, we will add Hegu (LI4), Sanyinjiao (SP6), Yinxi (HT6), and Xuehai (SP10). For qi and blood deficiency, we will add Qihai (CV6), Zhongwan (CV12), Zusanli (ST36), and Laogong (PC8). After *de qi*, the needles will be retained for 20 minutes. Other interventions, such as moxibustion, cupping, and herbs will not be used. The participants will receive a total of 14 sessions over 3 to 4 weeks (3 to 4 sessions per week).

**Figure 1 Fig1:**
[figure not shown]
Directions of acupuncture interventions. When acupuncture is initiated at the left Fengchi (GB 20), it will proceed toward the right outer canthus or the Adam’s apple. When acupuncture is initiated at the right Fengchi (GB 20), it will proceed toward the left outer canthus or the Adam’s apple.

### Outcome measurement

Outcome measurements will be assessed at baseline and after the treatment phase. We will use multiple outcome measurements, including subjective and objective parameters.

The patients will be required to complete several subjective questionnaires before and after treatment, including the following: the Vertebrobasilar System Ischemic Neurological Impairment Scale (VBS-INIS) (range: 0 to 22) [17], UCLA Dizziness Questionnaire (UCLA-DQ) (range: 5 to 25) [18], Activities of Daily Living Scale (ADL) (range: 14 to 56) [19], and Psychological and Social Adaptation Scale (range: 0 to 20) [20]. All scales have been validated in previous studies.

The VBS-INIS assesses the degree of neurological impairment caused by vertebrobasilar ischemia. Common signs and symptoms include dizziness, deafness or tinnitus, double vision, dysarthria, or swallowing impairment. The scale was demonstrated to be uniform, stable, and reliable. Higher scores indicate more severe damage.

The UCLA-DQ is used to measure the severity and frequency of dizziness. The questionnaire contains five items to evaluate the patients in terms of daily activity, quality of life, and their fear of dizziness.

The ADL is a validated questionnaire that has been widely used to assess ability of an individual to function in daily life. The questionnaire consists of two parts: the Physical Self-Maintenance Scale and the Instrumental Activities of Daily Living Scale.

The Psychological and Social Adaptation Scale mainly describes the impact of dizziness on daily life and work. The scale assesses psychological parameters, such as temper, worry, fear, quality of sleep, and communication with others. The reliability, availability, and sensitivity of this scale had been clinically tested [20].

Objective parameters will also be used to compare differences in cerebral blood flow via TCD and carotid ultrasonography. Changes in cerebral oxygenation will be investigated using near-infrared spectroscopy, and the inherent mechanism underlying acupuncture treatment efficacy will be investigated using metabolomics (Figure 2).

**Figure 2 Fig2:**
[figure not shown]
Study sequence. A total of 144 eligible participants will be randomized into one of four treatment groups receiving acupuncture for one minute with different manipulation parameters. Group 1 will receive twirling with a frequency of 60 times per minute toward the contralateral outer canthus at a depth of 0.5 to 0.8 cun. Group 2 will receive twirling with a frequency of 60 times per minute toward the Adam’s apple at a depth of 0.5 to 0.8 cun. Group 3 will receive twirling with a frequency of 120 times per minute toward the contralateral outer canthus at a depth of 0.5 to 0.8 cun. Group 4 will receive twirling with a frequency of 120 times per minute toward the Adam’s apple at a depth of 0.5 to 0.8 cun. The participants will receive 14 acupuncture sessions over 3 to 4 weeks. The subjects will be assessed at two time points: baseline and post-treatment. The primary outcome measurements will include subjective measurements (Vertebrobasilar System Ischemic Neurological Impairment Scale, UCLA Dizziness Questionnaire, Activities of Daily Living Scale, and Psychological and Social Adaptation Scale) and objective measurements (Transcranial Doppler, carotid ultrasonography, and changes in cerebral oxygenation) to reduce bias arising from the placebo effect. We will use metabolomics to investigate the mechanisms underlying the effects of the different manipulation parameters.

Certain medical assessments, such as general information, vital signs, symptoms, physical signs, previous history, complications, and information from the TCM diagnosis, will also be recorded.

### Patient safety

Patient safety will be assessed using laboratory tests (for example, routine blood, urine and feces tests, and hepatic and renal function) and electrocardiography before and after treatment. These tests will also be used to identify potential side effects. For every session of acupuncture, curative effects, duration, syndrome, adverse reactions or events (for example, bleeding, hematoma, or serious pain), and patient dropout will be recorded. If any patients experience adverse events, follow-up monitoring will be performed until the adverse events resolve.

### Quality control

Different factors have been considered to reduce bias. All researchers are trained to diagnose posterior circulation ischemia, to observe and record data, and to fill in the case report forms. During the trial, supervisors will regularly audit the trial to verify the consistency of the raw data and the recorded data. The data analyst will be involved early on in the study, so that the entire trial can be monitored.

### Statistical analysis

#### Sample size

We estimated the sample size using a formula, as was performed in relevant literature studies. We plan to enroll a total of 144 participants, with 36 individuals in each group, allowing for a 20% withdrawal rate.

#### Analysis strategy

Statistical analysis will be performed using the statistical software package SPSS 16.0 for Windows (SPSS Inc., Chicago, IL, USA). Differences between the baseline characteristics of each treatment group will be analyzed using an analysis of variance (ANOVA) for continuous variables such as age, body mass index, and disease course. Comparisons among the baseline characteristics of the four groups for categorical variables, such as gender and medical history, will be made using the chi-square test. Paired sample *t*-tests will be used to compare the subjective and objective outcome measurements before and after treatment. Comparisons of the subjective and objective outcome measurements among the four groups will be performed by ANOVA. A *P* value of less than 0.05 will be considered statistically significant. Qualified statisticians will perform the statistical analyses in a blinded manner.

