This study includes some limitations that may affect the results. First, we will not conduct a follow-up study. We consider the observation of the short-term therapeutic clinical effects sufficient to investigate our hypothesis, but our study design is insufficient for evaluating long-term effects. Moreover, the outcome measurement scales may contain bias when translated into Chinese, which could influence the results of the trial. Furthermore, because Chinese patients expect acupuncture to be effective, the placebo effect may exert a stronger influence on the results than if the study is performed with mostly Western patients. To reduce this bias, we will use multiple outcome measurements, including subjective and objective outcome measurements. The placebo effect might significantly influence subjective outcomes but should not significantly affect objective measurements [31]. Finally, we did not use sham acupuncture. Because Chinese patients generally trust acupuncture, informed consent for the use of sham acupuncture is difficult to obtain [32]. A previous study also demonstrated that acupuncture is an effective intervention for PCIV; therefore, we want to compare different acupuncture methods [8].

The results of this study may help explain the contradictory results obtained from acupuncture studies if the different manipulations can induce different treatment effects [33]. This study could also elucidate the overall treatment effect of acupuncture on patients with PCIV. The use of both subjective and objective outcome measurements should allow the identification of significant differences between these two outcome measurements.

In conclusion, this study will attempt to explore the relative efficacies of different acupuncture manipulations and their mechanisms of action. Because the focus of this study is highly specific, the findings may have implications for a number of ongoing debates in the field of acupuncture research.

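### Disease course is recorded, and no limit on time since onset is set, but the stated outcome ANOVA leaves it out; this costs some precision if it predicts change over 3 to 4 weeks

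*Protocol article*

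**What the plan says.** The Diagnostic criteria section of the protocol article reads: "Patients must experience dizziness or vertigo that may be accompanied by the following: acute unsteadiness or ataxia". Other acute signs follow as optional features, and imaging evidence is required. The inclusion list asks for "Diagnosis of vertebrobasilar insufficiency", age 40 to 75, willingness to be treated and consent. The exclusion list removes some severe acute presentations, for example a Glasgow Coma Scale score below 15. None of the three lists gives a time since onset or a symptom duration.

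Randomization is described thus: "Patients will be consecutively and randomly assigned to one of four groups in a 1:1:1:1 ratio". No stratification factor is mentioned. Assessments are at baseline and after a course of 3 to 4 weeks. The Discussion states that there is no follow-up.

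The Analysis strategy section uses ANOVA to compare baseline characteristics "for continuous variables such as age, body mass index, and disease course". It then names ANOVA again for comparing the subjective and objective outcomes among the four groups, and mentions no covariate. Disease course appears nowhere else in the article.

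**The concern.** A patient whose symptoms began recently may improve over a few weeks whatever manipulation is used, while a patient with a stable complaint of years may not. If so, duration is prognostic for the change that the trial measures. The trial compares four active manipulations with each other, so the differences sought may be small and precision matters.

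Testing disease course for baseline differences between randomized groups does nothing for the precision of the outcome comparison. Using it as a covariate in the outcome model would help. As the article stands, a recorded variable that is plausibly prognostic goes to the first use and not the second. What is at stake is interval width and power, not validity.

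**Working it through.** **The plan's own figures.** The Sample size section says: "We plan to enroll a total of 144 participants, with 36 individuals in each group, allowing for a 20% withdrawal rate". The total is consistent: 4 × 36 = 144. After 20% withdrawal, 36 × 0.8 = 28.8, about 29 completers per arm. The effect size, SD and power behind 36 are not given, so the number itself cannot be re-derived, and this point does not depend on it.

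**Assumptions, not document figures.**
- Share of early-onset patients: q = 0.3 (range 0.1 to 0.5).
- Extra spontaneous improvement in early-onset patients: d = 0.5 to 1, in units of the SD within an onset group. A value of 1.5 is shown as an extreme.
- Two-sided testing at the stated 0.05 level (the article does not state sidedness).

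**Variance share.** With within-group variance 1, the mix adds q(1−q)d².
- d = 0.5: 0.3 × 0.7 × 0.25 = 0.0525; share 0.0525/1.0525 = 5%.
- d = 1: 0.3 × 0.7 × 1 = 0.21; share 0.21/1.21 = 17%.

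**Interval width.** Without the mix, the half-width for a difference between two arms is 1.96 × √(2/29) = 0.51 SD. With the mix unadjusted it is multiplied by √(1 + q(1−q)d²).
- d = 0.5: √1.0525 = 1.026; half-width 0.53 SD, about 3% wider.
- d = 1: √1.21 = 1.10; half-width 0.57 SD, 10% wider.

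Over q = 0.1 to 0.5 and d = 0.5 to 1, the multiplier runs from 1.011 to 1.118.

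**Power.** Take a pairwise difference that would have 80% power without the mix at 29 per arm (0.736 SD). Pairwise power with the mix unadjusted, for q from 0.1 to 0.5:

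| d | Power |
|---|---|
| 0.5 | 77.6% to 79.1% |
| 1.0 | 70.7% to 76.5% |
| 1.5 | 61.1% to 72.4% |

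Full adjustment would return power to about 80%. Adjustment with an imperfect duration measure recovers only part of the loss.

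**Chance imbalance.** The 95% range of the between-arm difference due to onset imbalance alone is 1.96 × d × √(2 × 0.21/29), which is 0.12 SD for d = 0.5 and 0.24 SD for d = 1. This is not an extra error on top of the intervals above. For d = 1, √(0.51² + 0.24²) gives about 0.57, the half-width already found. The unadjusted standard error contains it.

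**The case against.** **Covariates may sit in an unseen analysis plan.** This is fair, and if that plan already adjusts for disease course the point is met. But the article is not silent here: it names the method for the outcome comparison and names the use of disease course, and the two do not meet.

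**The trial is declared pragmatic, so a broad mix of durations suits it.** This stands as a reason not to criticize eligibility, and recruitment had finished in August 2014 in any case. It is no reason to leave a recorded predictor out of the model. Mixing is permitted by the criteria but not shown to have occurred.

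**Disease course is not defined.** It may mean total illness duration and not time since the current episode. This stands and limits the expected gain.

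Three stronger readings are tempting, but the article does not support them.

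- *A reader might infer that spontaneous recovery drives all arms to the floor of the scales.* No baseline scores or recovery rates are given. In an illustrative simulation (0 to 22 scale, SD 3, average fall 3 points, 4 more in early-onset patients, true difference 2.2 points, up to 50% early-onset), a baseline mean of 12 put only 0% to 3% of the reference arm at zero and left the difference at 2.1 to 2.2. Material compression needed low baseline scores. A floor could touch only the four questionnaires, not Doppler, carotid ultrasonography or cerebral oxygenation, and a covariate would not undo it.
- *A reader might infer that onset imbalance produces spurious differences.* Onset precedes randomization, so imbalance is random and already inside the standard error.
- *A reader might want results split by recent and long-standing onset.* At 30% early-onset, 0.3 × 29 is about 9 completers per arm, across seven primary measures. That table would be too noisy to inform.

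**Conclusion.** The point holds as a modest loss of precision. The criteria allow recent and long-standing cases together, and the stated outcome ANOVA does not use the recorded duration. Under the central assumptions (30% early-onset, 0.5 to 1 SD extra improvement), between-arm intervals are about 3% to 10% wider than they need be. That size rests wholly on the assumed onset mix and recovery. It shrinks if disease course is weakly prognostic or if the baseline score already carries much of the same information. The unadjusted comparison remains valid: there is no bias between arms and no inflated false-positive rate. Floor compression is a conditional possibility, not a finding.

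**What to change.** In the Analysis strategy section, replace the between-group outcome ANOVA with an ANCOVA that has treatment group as factor and two covariates: the baseline value of the outcome and disease course, log-transformed if skewed. State how disease course is measured, and fix the model before unblinding.

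The cost is one or two degrees of freedom. With 4 × 29 = 116 completers, residual degrees of freedom go from 116 − 4 = 112 to 110. No new data are needed. The downside is little gain if disease course turns out to be weakly prognostic. No change to eligibility is asked for.

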## Background

Vertigo is the main symptom of posterior circulation ischemia (PCI) [1]. Patients with vertigo resulting from posterior circulation ischemia (PCIV) are mainly middle-aged or older, and most patients are male [2]. The most common causes of PCI are atherosclerotic lesions, embolism, and small penetrating arterial disease, which lead to tissue function defects of the inner ear, brainstem, and cerebellum [2-5].

Traditional Chinese medicine (TCM) theorizes that vertigo is caused by a loss of nourishment in the upper orifices resulting from pathogenic wind, heat, phlegm, deficiency, or stasis. Vertigo is thought to be closely related to the liver, kidney, heart, and spleen [6]. Fengchi (GB 20) is one of the main acupoints used to treat vertigo, and acupuncture at Fengchi (GB 20) promotes the flow of qi and blood, pacifies the liver, and normalizes bile secretion [7]. Our previous study found that needling at Fengchi (GB 20) could improve cerebral blood flow in patients with PCIV [8].

Recent human and animal experiments have indicated that different needling manipulations could result in different effects through different physiological mechanisms [9,10]. However, few studies have investigated the influence of different needling directions and frequencies and their inherent mechanism of action.

We hypothesize that an ideal quantity of stimulation applied at Fengchi (GB 20) may induce an optimal effect in PCIV patients. This hypothesis is based on the quantity theory of acupuncture manipulation developed by academician [name], who stated, ‘acupuncture is an intervention for physical stimulation; so the quantity of stimulation including the intensity, frequency, duration, direction of the needle tip, and interval between intervention sessions may play a vital role in clinical outcomes. Just as with drugs, the effect of acupuncture is derived from the quantity of intervention. The optimal effect of acupuncture depends on the optimal stimulation quantity. Therefore, acupuncture intervention should be clearly quantified in clinical acupuncture research.’ In this study, we aim to explore whether different needling manipulations (direction and frequency) at Fengchi (GB 20) can influence the clinical effects of acupuncture via different physiological mechanisms. We also aim to investigate the most effective acupuncture parameters in patients with PCIV.

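### The arms form a complete 2x2 of direction by frequency, but the stated four-group ANOVA isolates neither factor nor their interaction

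*Protocol article*

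**What the plan says.** In the Protocol article, Background, the first aim is to "explore whether different needling manipulations (direction and frequency) at Fengchi (GB 20) can influence the clinical effects of acupuncture". A second aim follows: "We also aim to investigate the most effective acupuncture parameters in patients with PCIV".

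The section on the rationale for acupoint selection presents direction (contralateral outer canthus or Adam's apple) and frequency (60 or 120 per minute) as two separately chosen variables. Protocol for acupuncture manipulation then assigns every combination. Group 1 is 60/canthus, Group 2 is 60/Adam's apple and Group 3 is 120/canthus. The last cell reads: "Group 4 will receive twirling with a frequency of 120 times per minute toward the Adam’s apple at a depth of 0.5 to 0.8 cun". Depth range and the one minute of twirling are the same in all four, and Randomization gives a 1:1:1:1 ratio.

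Analysis strategy gives one between-group method for the outcomes: "Comparisons of the subjective and objective outcome measurements among the four groups will be performed by ANOVA", at P below 0.05. It names no factor, main effect, interaction or contrast. Acupuncture groups describes the design in the same flat way: "We will use a pragmatic design to directly compare four parameters".

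**The concern.** The design and the first aim are built on two factors, while the stated analysis is built on four arms. A significant four-group F test says that at least one arm mean differs from another. It does not say whether direction matters, whether frequency matters, or whether the effect of one depends on the other. A non-significant result is no clearer, because a real effect of one factor is tested together with two further degrees of freedom that carry no signal.

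The main strength of a 2x2 layout also goes unused. Each factor can be estimated from all patients, half at each level, rather than from separate arms. At stake is whether the trial can answer its first question directly, and with the precision that its sample size allows.

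**Working it through.** **Inputs from the Protocol article.** 144 patients, 36 per group, 20% withdrawal (Sample size); 1:1:1:1 allocation (Randomization); alpha 0.05 (Analysis strategy).

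**The plan's own figure.** 4 x 36 = 144, which agrees. After withdrawal, 36 x 0.8 = 28.8, taken as n = 29 per group, so N = 116 and the error df are 116 - 4 = 112. The article gives no effect size, SD or power, so the 36 itself cannot be re-derived.

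**Assumptions.** Effects are in SD units. The main case is 0.5 SD, with a range of 0.4 to 0.6. Variances are equal and there is no baseline adjustment.

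**Formulas.** Power is the probability that a noncentral F exceeds its critical value.
- Four-group test: df 3 and 112, noncentrality = n x sum of (cell mean - grand mean)².
- Factor or interaction contrast L: df 1 and 112, noncentrality = n x (sum of L x mean)² / (sum of L²).

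**One factor acts (cell means 0, 0, d, d).** At d = 0.5:
- Four-group: 29 x 4 x 0.25² = 7.25.
- Factor contrast with L = (-1, -1, 1, 1): 29 x 1.0² / 4 = 7.25.

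The signal is the same, but it is spread over 3 df in one test and concentrated in 1 df in the other. The critical values are 2.69 for the four-group test, 3.93 for the contrast at alpha 0.05, and 5.16 for the contrast at 0.025.

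| Assumed effect | Four-group F | Factor contrast, 0.05 | Factor contrast, 0.025 |
|---|---|---|---|
| 0.4 SD | 40% | 57% | 46% |
| 0.5 SD | 59% | 76% | 66% |
| 0.6 SD | 76% | 89% | 83% |
| Detectable at 80% power | 0.62 SD | 0.52 SD | 0.58 SD |

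The 0.025 column is the fair comparison if alpha is split equally over the two main effects. At 0.5 SD the gain is then 66 - 59 = 7 points, rather than 76 - 59 = 17.

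**Other patterns, n = 29 per group.**
- Both factors act additively at 0.5 SD (means 0, 0.5, 0.5, 1.0). The four-group noncentrality is 29 x (0.25 + 0 + 0 + 0.25) = 14.5, giving 90% power. Each factor contrast has 76% (66% at 0.025).
- Only one arm differs, by 0.6 SD. The four-group noncentrality is 29 x (3 x 0.15² + 0.45²) = 7.83, giving 63%. Each 1-df contrast has 29 x 0.6² / 4 = 2.61, giving 36% (26% at 0.025).

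**Interaction.** For a pure interaction with a difference of differences of 1.0 SD, the four-group test has 59% and the 1-df interaction contrast 76%. Reaching 80% needs about 1.05 SD, twice the detectable main effect at alpha 0.05.

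**The case against.** The strongest reply is that the text says ANOVA, not one-way ANOVA. A two-factor model is also an ANOVA on the same four groups, and a separate analysis plan, not shown, may set out its terms. A reader might infer that the trial will certainly test neither factor; the article does not establish that. Still, it does more than stay silent. It names the four groups as the unit of comparison and describes the design as a direct comparison of four parameters. The four-group reading is a strong inference, and the sentence needs correcting even if a two-factor model was meant.

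A reader might also infer that the four-group test loses power throughout. It does not. If both factors act, or only one arm stands out, it is more likely than any single contrast to reject the hypothesis that all arms are equal. The one-arm pattern is close to the hypothesis in Background that an ideal quantity of stimulation gives an optimal effect. The second aim, finding the most effective parameters, therefore makes a four-arm comparison legitimate. This stands, and is why that comparison should be kept. It does not help the first aim, because a global rejection still attributes nothing to direction or frequency.

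Finally, a reader might expect a series of unadjusted pairwise tests between arms to follow. Analysis strategy plans none, so the plan cannot be faulted for their power or multiplicity.

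**Conclusion.** The point holds as a mismatch between a factorial design with an aim stated by factor and an analysis that, as written, isolates neither factor nor their interaction. For an assumed effect of one factor alone, naming the factors raises power at 0.5 SD by 17 points at the full alpha, or by about 7 points with alpha split. The benefit is attribution together with power for a named factor; it does not extend to the global null.

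The figures rest on 29 evaluable patients per group and on assumed effects, since the article states none. The qualitative point does not depend on them. Nothing in the stated analysis biases an estimate, the aims are worded as exploratory, and the data as designed support the better model. This should be fixed, but it does not threaten the trial's validity.

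**What to change.** Replace the between-group sentence in Analysis strategy with a two-factor linear model containing direction, frequency and direction x frequency. Report each 1-df main effect and the interaction with 95% CIs, and split 0.05 or apply Holm over the two main effects. Keep the four-arm comparison, and the four cell means with CIs, as the secondary analysis for the aim of finding the most effective parameters.

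The cost is wording only. Trial status says recruitment has finished, so the analysis is the part that can still change, and the change should be made before unblinding. It needs the same data and the same software. The small downside is that each main effect averages over the other factor, which can mislead if one combination is best. The interaction is weakly powered, so its estimate must stand beside the main effects, and a non-significant interaction should not be taken as evidence that there is none.
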